### Statistical analysis

#### Descriptive analysis

Patients will be described according to their initial treatment group attributed after the randomization. A flowchart of enrolled and analysed patients will be provided. Demographic, clinical, and biological characteristics recorded at time of randomization will be described. Descriptive analyses will use numbers (percentages) for qualitative variables, mean ± standard deviation or median (first to third quartiles) as appropriate for quantitative variables, and Kaplan-Meir curves or cumulative incidences in the presence of competing risks for time to event. No statistical test will be formally performed to compare the initial characteristics of randomized groups.

#### Statistical analysis

The ITT analysis will involve data on all patients in each dose group. All patients who are lost to follow-up for any reason will be treated as failures at the time of last contact or at the time of an event that results in discontinuation, whichever occurs first. The per-protocol set will exclude from the full analysis the set non-compliant patients, patients who received less than 50% of the treatment, and patients who received concomitant administration of an excluded treatment.

All events occurring during the 2 years of follow-up will be recorded. The principal criteria (occurrence of the first event constituting the composite endpoint) will be compared between the two groups using the Cox model that takes into account the stratification by the centre. Secondary criteria will be compared using tests corresponding to the nature of the variable: *χ*^2^ or Fisher’s exact test for qualitative variables, parametric or non-parametric variance analysis for quantitative variables, and log-rank or Gray’s test for time to event. The secondary parameters that will be analysed are the following: the incidence of each of the events constituting the composite primary endpoint; BP measurement, and number, drug classes and doses of antihypertensive drugs necessary to reach normal BP; preventive coronary revascularisation; evolution of the left ventricular ejection fractions and of the left ventricular wall thickness assessed by transthoracic echocardiography; vitamin D insufficiency correction; evolution of the fasting urinary calcium/creatinine ratio and of serum calcium, phosphate, and PTH concentrations; bone fracture incidence; changes in body height; changes in bone mineral density at the lumbar spine and femoral neck; incidence of infectious episodes and type of infection; incidence of treated acute rejection episodes; evolution of MDRD eGFR, of urinary protein/creatinine ratio, and of urinary microalbuminuria/creatinine ratio; graft survival; evolution of HbA1C in the absence of DM; evolution of HbA1C and of anti-diabetic treatments in cases of *de novo* DM; or incidence of cholecalciferol-related side effects (hypercalcaemia, calcic nephrolithiasis and other spontaneously reported side effects). Adjustment for multiple testing will be performed using the Hochberg procedure for the components of the primary criteria. We will also describe in detail each adverse event (AE) that occurs during the study, and we will report the overall rate of occurrence of AE, the rate of withdrawal from the study due to an AE, the overall rate of patients with at least one clinically significant laboratory abnormality, the rate of AEs attributable to treatment (possible or probable relationship), and the rate of serious AEs. The percentage of patients with each of the AEs associated with cholecalciferol and the intensity of these AEs will be specified.

Some additional p*ost hoc* subgroup analyses will also be performed (according to, for example, baseline 25OHD levels, achieved 25OHD levels, VDR and vitamin D binding protein polymorphisms, and corticosteroid treatment, among others).

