### Study population and sample size

The study sample will consist of 640 RTRs found to be lacking sufficient vitamin D (25OHD <30 ng/ml) 12 to 48 months post-transplantation with 320 subjects in each study group. Inclusion and exclusion criteria are detailed in the Appendix. The sample size calculation was performed according to the following assumptions: The principal criteria will be the occurrence of one of the events of the composite endpoint including *de novo* DM, major cardiovascular events, *de novo* cancer, and patient death. Over a 2-year follow-up period, we estimate, according to previous reports in the literature, that the incidence of a first event of the composite endpoint will be around 22% in our population (6% for *de novo* T2DM [91, 92], 6% for major cardiovascular events [93–95], 7% for *de novo* cancers [15, 96], and 3% for patient death). This 22% global estimated incidence does not take into account the fact that some patients may experience several events of the composite endpoint during the follow-up period. According to the results of the numerous observational studies showing an inverse association between 25OHD concentrations and various clinical events and to the results of the few interventional trials showing effects of high-dose vitamin D supplementation on these events (detailed above),we estimate that the overall decrease in the incidence risk of a first event of the composite endpoint will be around 40% in the high-dose group compared with the low-dose group (33% decrease for *de novo* DM, 40% decrease for major cardiovascular events and 50% decrease for *de novo* cancer). Thus, to demonstrate the reduction in the incidence of a first event of the composite endpoint from 22% in the low-dose group to 13% in the high-dose group, with a 90% power and 5% α risk error, 582 RTRs (291 in each group) will be required. Taking into account that 10% of patients will not be evaluable, a total of 640 RTRs will be required. The inclusion of a total of 480 RTRs would allow us to test the same hypothesis with a power of 80%.

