The two side effects caused by vitamin D_3_ that may occur are increase in serum calcium levels or in urinary calcium excretion. At serum calcium levels >2.85 mmol/l, serum phosphate levels >1.8 mmol/l or in cases of major increase in urinary calcium excretion (increase in fasting baseline urinary calcium/creatinine ratio ≥0.4 mmol/mmol in the absence of furosemide introduction), the aforementioned monthly vitamin D_3_ administration will be discontinued. If the biological abnormalities cited above persist after vitamin D_3_ re-introduction, cholecalciferol treatment will be halted. Cholecalciferol treatment will be immediately discontinued in cases of proven graft nephrolithiasis (except for uric acid calculi, whose composition has been proven by calculi analysis) or nephrocalcinosis, symptomatic hypercalcemia, or pregnancy occurrence. VITALE is an ITT study. Consequently, in cases of cholecalciferol discontinuation, patient follow-up will be maintained according to the study guidelines until the end of the 24 month follow-up period.

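### Counting every patient lost to follow-up as a failure adds non-events to the primary Cox analysis, costs power, and can bias the hazard ratio in either direction

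*Protocol article*

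**What the plan says.** The protocol article, under Statistical analysis, sets the rule within its description of the ITT analysis: "All patients who are lost to follow-up for any reason will be treated as failures at the time of last contact". The sentence goes on to give an alternative date: "or at the time of an event that results in discontinuation, whichever occurs first".

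The next paragraph names the primary comparison: "The principal criteria (occurrence of the first event constituting the composite endpoint) will be compared between the two groups using the Cox model", with stratification by centre taken into account. Objectives and Study population and sample size both list four components: de novo diabetes, major cardiovascular events, de novo cancer and death. Loss to follow-up is in neither list.

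Two other sections bear on the rule. Study intervention says that "in cases of cholecalciferol discontinuation, patient follow-up will be maintained according to the study guidelines until the end of the 24 month follow-up period". Study population and sample size plans for a reduction "from 22% in the low-dose group to 13% in the high-dose group, with a 90% power and 5% α risk error", and then enlarges the sample on the ground that "10% of patients will not be evaluable".

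**The concern.** A patient who moves away or withdraws consent has not thereby had diabetes, a cardiovascular event, cancer or death. Inclusion visit lets patients withdraw at any time without giving a reason, so losses for any reason include losses unrelated to outcome. A Cox model can handle such a patient by censoring at last contact. The stated rule records an event there instead.

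The rule also fits poorly with the sample-size section. That section sets aside 10% as not evaluable, whereas the rule makes lost patients evaluable, as failures. The 22% and 13% contain composite events only, so the contrast analysed would differ from the contrast powered.

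The primary estimate and its test are at stake. If loss is equal, the hazard ratio moves towards 1 and power falls. If loss is unequal, the difference in loss enters the hazard ratio as though it were a treatment effect. Objectives also makes the safety of the high-dose scheme a main question, so a spurious shift towards harm would matter as much as one towards benefit.

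**Working it through.** **Inputs from the document.** Two-year incidence 22% (low dose) and 13% (high dose), 90% power, 5% alpha with sidedness not stated, 582 evaluable, 640 in total, 1:1 allocation, two years of follow-up.

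**Assumptions.** Constant hazards; loss independent of outcome; 320 per arm; two-sided 5% unless stated. No loss rate is given. The 10% non-evaluable figure is used as the top of the equal-loss range, with 2% and 5% below it.

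**The plan's own figure.** The yearly hazards are −ln(0.78)/2 = 0.1242 and −ln(0.87)/2 = 0.0696, so the design hazard ratio is 0.0696/0.1242 = 0.56. Schoenfeld's formula gives events = 4(z_α + z_β)²/(ln HR)². At one-sided 5% and 90% power this is 4(1.645 + 1.282)²/(0.579)² ≈ 102 events. Divided by the mean incidence of 0.175, that is N ≈ 584, close to 582. At two-sided 5% the same route gives about 717 before rounding. Also, 582 × 1.10 = 640. One-sided power is therefore given below as a cross-check.

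**Effect of the rule.** For a loss proportion d over two years, the loss hazard is μ = −ln(1 − d)/2. Loss counts as failure, so:

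- counted HR = (0.0696 + μ_high)/(0.1242 + μ_low)
- counted proportion in an arm = 1 − exp(−2(λ + μ)), of which the share λ/(λ + μ) is true events
- power = Φ(√events × |ln HR|/2 − 1.96)

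**Worked case, 10% loss in each arm.** μ = −ln(0.9)/2 = 0.0527. HR = 0.1223/0.1769 = 0.69. Counted proportions are 29.8% and 21.7%, so counted events are 320 × (0.298 + 0.217) ≈ 165. True events are about 106.5. The imputed share is (165 − 106.5)/165 ≈ 35%.

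**Equal loss**

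| Loss per arm | Counted events | True events | HR under the rule | Power under the rule | Power with censoring |
|---|---|---|---|---|---|
| 2% | 123 | 111 | 0.59 | 82% | 86% |
| 5% | 138 | 109 | 0.64 | 76% | 86% |
| 10% | 165 | 106 | 0.69 | 66% | 85% |

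A 2,000-run log-rank simulation at 10% loss gave 65% under the rule and 83% with censoring. At one-sided 5%, power at 10% loss is 77% under the rule and 91% with censoring.

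**Unequal loss** (for 5%, μ = 0.0256)

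| Loss, low / high dose | HR if true HR is 0.56 | HR if no true effect |
|---|---|---|
| 5% / 10% | (0.0696 + 0.0527)/(0.1242 + 0.0256) = 0.82 | (0.1242 + 0.0527)/(0.1242 + 0.0256) = 1.18 |
| 10% / 5% | (0.0696 + 0.0256)/(0.1242 + 0.0527) = 0.54 | (0.1242 + 0.0256)/(0.1242 + 0.0527) = 0.85 |

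In the first row, two-sided power for the planned effect is about 24%.

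**The case against.** **Size.** The article gives no loss rate. Its 10% is a non-evaluable share, which need not be loss to follow-up. At 2% loss per arm the cost is about four points of power. With equal loss and no true effect the hazard ratio stays at 1, so the rule then produces no excess of false positives. All of this stands, and it is why a range is shown.

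**The rule as a conservative convention.** Pre-specified failure imputation is sometimes defended as a cautious choice. That does not hold here. If the low-dose arm loses more patients, the rule exaggerates benefit (0.54 instead of 0.56) and creates apparent benefit where none exists (0.85).

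**A stronger reading.** A reader might infer that every patient who stops cholecalciferol because of an event is also a failure, so that stops for raised calcium in the high-dose arm would appear as harm. The text does not support this. The subject of the sentence is patients lost to follow-up, and the discontinuation clause most plainly only dates their failure. Study intervention keeps patients who stop treatment under follow-up to month 24, so stopping alone does not make them lost. Nor does the document say how much more often high-dose patients would stop; Risk analysis in the Discussion argues that high doses leave serum and urinary calcium unaffected.

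What remains is an ambiguity. The article does not say whether discontinuation means leaving the study or stopping treatment. Even on the plain reading, a patient who stops treatment for an event outside the composite and is later lost could be failed at that earlier date.

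**Conclusion.** The point holds for loss to follow-up. The rule as written counts as primary events something the endpoint definition excludes, and nothing else in the article corrects it. Because it is a stated rule, it is not a detail left to an unseen analysis plan.

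With equal loss of 2% to 10% per arm, the planned hazard ratio of 0.56 would appear as 0.59 to 0.69, at a cost of roughly 4 to 19 points of two-sided power. A five-point imbalance in loss moves the hazard ratio to 0.82 or 0.54 depending on direction, or to 1.18 or 0.85 if the treatment does nothing. These sizes rest on assumed loss rates, constant hazards and loss unrelated to outcome. That non-events enter the primary analysis rests on none of these assumptions.

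The article does not establish that treatment stops are themselves counted as failures. That part is a request for clarification.

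**What to change.** In Statistical analysis, replace the failure rule for the primary ITT Cox analysis: only true composite events count, and patients without one are censored at last contact or month 24. Keep lost-as-failure as a named sensitivity analysis, since censoring assumes that loss is unrelated to outcome, and report the number and timing of losses by arm.

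Separately, state whether discontinuation in this rule means study or treatment discontinuation, and reconcile it with Study intervention, so that patients who stop treatment but remain in follow-up contribute only their true composite events.

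The cost is a sentence or two of text. No further data are needed: contact dates and composite events are already recorded over the two years. With censoring, the sample-size rates again describe the quantity being analysed.

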### Randomization and blinding

If all inclusion and none of the exclusion criteria are met and informed consent has been obtained, each RTR will be included in the study and allocated a randomization number used for assignment to one of the two treatment arms. The randomization list will be computer-generated and created using nQuery Advisor software (v6.01). The randomization will be stratified by centres, and blocks of four will be used in order to facilitate treatment distribution by the central pharmacy. The size of the blocks will be unknown to the investigators. The two treatment regimens will be randomly allocated in a 1:1 ratio. The attribution arm will be given centrally by Cleanweb® software after the validation of inclusion criteria, and this software also allows entering trial data for each patient. Participants, investigators, and outcome assessors will be blinded to the allocated treatment. Blinding will be ensured by the use of investigational products that are identical in packaging, labelling, appearance, smell, and taste. Unblinding will occur only in cases of emergency or at the conclusion of the study. In most cases, discontinuation of the treatment should be sufficient without the need for unblinding. Access to the randomization list will be restricted to the pharmacist involved in the study and a research assistant.

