### Study procedure

#### Inclusion visit

At 12 to 48 months after kidney transplantation, each RTR found to have 25OHD levels below 30 ng/ml during a routine visit will be given information about the VITALE study, its purpose, putative benefits, and possible risks, and will be invited to participate in the trial. All patients will be informed that the participation in that study is voluntary, and that they may refuse to participate or withdraw from the trial at any time without giving reasons and without loss of benefits. RTRs who do not agree to participate in the study will receive standard care. If the RTR agrees, they will sign a written informed consent form, and demographic, clinical, and biological baseline data will be collected. In addition, daily calcium intake will be evaluated by means of a questionnaire.

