## Appendix

### Eligibility criteria

#### Inclusion criteria

 RTRs who are between 12 and 48 months after transplantation with stable renal function during the past 3 months Vitamin D insufficiency, defined as a concentration of 25OHD lower than 30 ng/ml Aged between 18 and 75 years old Capable of understanding the advantages and the risks of the study Have social security health insurance Have provided written informed consent

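### The primary Cox model names only centre; a short pre-specified list of baseline covariates would recover some power, by an amount that depends on how prognostic they are

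*Protocol article*

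**What the plan says.** Under Statistical analysis, the protocol article states that the occurrence of the first component event "will be compared between the two groups using the Cox model that takes into account the stratification by the centre". No further covariate is named and none is ruled out. Under Randomization and blinding, allocation is stratified by centre in blocks of four, and "The two treatment regimens will be randomly allocated in a 1:1 ratio".

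At the inclusion visit "demographic, clinical, and biological baseline data will be collected", and randomization follows within a week. Table 1 lists medical history, current treatment, blood pressure, fasting glycaemia, HbA1c, lipids and renal function at that visit. The population is broad: one inclusion criterion reads "Aged between 18 and 75 years old", and patients may be anywhere from 12 to 48 months after transplantation. The exclusion list does not remove prior cardiovascular disease or prior cancer.

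The sample size section plans for a fall "from 22% in the low-dose group to 13% in the high-dose group", and states that "with a 90% power and 5% α risk error, 582 RTRs (291 in each group) will be required".

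**The concern.** Several recorded variables plausibly predict the composite. Age bears on cardiovascular events, cancer and death. Fasting glycaemia at inclusion is an earlier measurement of one of the variables whose threshold defines de novo diabetes. Prior cardiovascular disease and prior cancer are admitted and vary between patients.

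When prognostic covariates are left out of a Cox model, the estimated hazard ratio lies closer to 1 than the covariate-conditional one. Adjustment slightly widens the standard error, but the estimate moves further from 1 by more than enough to compensate, so power rises. The planning rates give 291 × 0.22 + 291 × 0.13 = 64.0 + 37.8, or about 102 events. At that number a few points of power from data already collected are worth having. The stake is sensitivity of the primary test, not its validity.

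**Working it through.** **Inputs from the article.** Two-year risks 22% and 13%; 291 evaluable patients per arm; alpha 5% (sidedness not stated, taken as two-sided); 1:1 allocation in blocks of four within centre; 30 centres; two years of follow-up.

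**Input that is assumed.** The SD of the covariates' combined contribution to the log-hazard, varied from 0.3 to 1.0 (C-index about 0.58 to 0.75). As a guide, the hazard ratio between a patient one SD above and one SD below the mean is exp(2 × SD): 1.8 at 0.3, 2.7 at 0.5, 5.0 at 0.8 and 7.4 at 1.0.

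**Step 1: the plan's own figure.** The pooled two-proportion formula is

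n per arm = [1.960 √(2 × 0.175 × 0.825) + 1.282 √(0.22 × 0.78 + 0.13 × 0.87)]² / 0.09² = (1.053 + 0.684)² / 0.0081 = 373.

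That is 746 in total, not 582. With 291 per arm the two-sided power is 81.7%. On the log-hazard scale, HR = ln(0.87)/ln(0.78) = 0.560, and √(101.85/4) × 0.579 − 1.960 = 0.961, which gives 83.2%. The stated 582 does reproduce for 22% versus 12% (291.3 per arm, unpooled, two-sided, 90%). A one-sided 5% test of 22% versus 13% would give 88.9% at 291 per arm, but the article states no one-sided test. The base for the present point is therefore about 82%.

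**Step 2: gain from adjustment.** The simulation used 30 centres, blocks of four and administrative censoring at two years. Marginal risks were held at 22% and 13%. A centre-stratified Cox model was fitted without and with five baseline covariates, in 8,000 trials per row. The Monte Carlo standard error of each gain is about 0.2 to 0.4 points.

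| Assumed SD | Centre only | Adjusted | Gain (points) | Conditional HR |
|---|---|---|---|---|
| 0.3 | 81.7% | 82.2% | 0.5 | 0.558 |
| 0.5 | 82.4% | 83.0% | 0.6 | 0.552 |
| 0.65 | 81.5% | 83.6% | 2.0 | 0.546 |
| 0.8 | 81.5% | 85.1% | 3.6 | 0.537 |
| 1.0 | 81.8% | 87.7% | 5.9 | 0.522 |

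**Step 3: other simulation runs.** A separate set of 4,000 trials per setting, with centres of unequal size, gave 80.9/81.7/81.6% with centre only and 82.3/83.9/86.2% adjusted at SD 0.5/0.7/0.9. The gains are 1.4, 2.2 and 4.6 points. A further run, reported to whole percentages, gave 82/81/83/82% and 82/83/86/85% at SD 0.3/0.5/0.7/0.9, so gains of roughly 0, 2, 3 and 3. The runs agree on direction and order of size and differ by a point or so in any one cell.

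**Step 4: other base rates.** The article's component reductions, with no effect on death, give 6 × 0.67 + 6 × 0.60 + 7 × 0.50 + 3 = 14.12%. At 22% versus 14.12%, power goes from 69.0/69.1/70.1% to 70.5/72.2/74.9% at SD 0.5/0.7/0.9, gains of 1.5, 3.1 and 4.8 points. At 22% versus 12%, where the base is about 90%, the gains are 0.3, 1.0, 1.8, 2.9 and 3.7 points at SD 0.3, 0.5, 0.65, 0.8 and 1.0.

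**Step 5: validity.** With no treatment effect, rejection rates at SD 0.5/0.7/0.9 were 4.9/5.1/4.9% with centre only and 4.9/5.2/5.3% adjusted. Both tests hold their level.

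**The case against.** The case for leaving the plan alone is substantial.

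- **The analysis matches the design.** Centre is the randomization stratum and the model accounts for it. Type I error is correct. This stands: nothing is contradicted.
- **The article is condensed and the SAP is not shown.** Accounting for centre does not exclude other covariates. A reader might infer that the trial has decided to ignore its baseline data, and the article does not support that. It does fix how the primary comparison is made and names only centre, so a choice is there to be improved.
- **Prognostic strength is not documented.** A reader might infer that strong predictors are being discarded at a guaranteed cost in power. The article gives no hazard ratio, C-index or similar figure. The composite mixes four kinds of event, and some covariates bear mainly on one of them. Diabetes is excluded and selection requires fasting glycaemia below 7 mmol/l, so that covariate's range is cut. Weak prognosis, with a gain near zero, must stay in the range.
- **Chance imbalance.** A reader might infer that imbalance in age or prior disease would bias the hazard ratio. It would not: such imbalance is random error, already covered by the test and confidence interval.
- **Adjustment is not free.** It needs no new data or patients, but it changes the target from a marginal hazard ratio of 0.560 to a conditional one between 0.558 and 0.522, and it needs more pre-specification.
- **Priority.** The sample-size shortfall is larger. So is the rule that counts losses as failures: with 640 randomized and an assumed 10% lost, centre-only power was about 65%, and adjustment returned only 1 to 6 points. This stands.

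**Conclusion.** The point holds as a conditional efficiency improvement. The planned test is valid but probably not the most sensitive use of the data collected. At 22% versus 13% with 582 patients, two-sided 5%, adjustment raises power from about 82% by about 0 to 1 point (SD 0.3 to 0.5), 2 to 4 points (0.65 to 0.8) or 4 to 6 points (0.9 to 1.0). The result rests on the assumed SD, on a two-sided test and on reading the centre term as stratification of the baseline hazard. Even the upper end does not bring 582 patients to the stated 90%: the highest adjusted figure is 87.7%. It is a cheap improvement, not an error to be corrected.

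**What to change.** Before unblinding, specify the primary analysis as a Cox model stratified by centre with a short fixed list of baseline covariates: age, history of cardiovascular disease, history of cancer, fasting glycaemia at inclusion and time since transplantation. State in advance how each is coded (continuous or categorical, and in what form) and how missing baseline values are handled. Keep the centre-only model as a sensitivity analysis, so that the hazard ratio closest to the planning assumption is also reported. If an existing SAP already lists covariates, reconcile it with the article's description.

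The cost is a sentence or two in the analysis section, with no new measurements or patients. The report must say that the primary hazard ratio is conditional on the covariates and can be expected to lie slightly further from 1 than the marginal one. The sample-size statement still needs its own correction.

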### Study design and setting

The VITALE study is a prospective, multicentre, double-blind, randomized trial with two parallel groups. Patient recruitment, kidney transplants, postoperative care, and follow-up are currently conducted in 30 transplantation departments in France, and there are about 2,700 kidney transplantations performed each year in France. In the absence of vitamin D supplementation, approximately 80% of RTRs are expected to have insufficient vitamin D. Of these patients, 20% to 30% are expected to fulfil the inclusion criteria and to agree to participate in the study. Consequently, the recruitment phase will last approximately 2 years, with a follow-up period of 2 years for each subject. The flowchart of the VITALE study is shown in Figure 1.

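### Quantitative secondary outcomes are compared by analysis of variance with no baseline covariate or centre term, which loses some precision but does not bias the comparison

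*Protocol article*

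**What the plan says.** Under Statistical analysis, the protocol article chooses the test for each secondary outcome by type of variable:

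- **Qualitative:** chi-square or Fisher's "exact test for qualitative variables".
- **Quantitative:** "parametric or non-parametric variance analysis for quantitative variables".
- **Time to event:** "log-rank or Gray’s test for time to event".

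No baseline covariate and no centre term is named for any of them. For the primary composite, the same paragraph specifies "the Cox model that takes into account the stratification by the centre". This matches Randomization and blinding: "The randomization will be stratified by centres, and blocks of four will be used".

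The list of secondary parameters words most quantitative outcomes as an evolution or a change: ejection fraction, wall thickness, urinary calcium/creatinine ratio, serum calcium, phosphate, PTH, eGFR, urinary protein and microalbumin ratios, HbA1c, body height and bone mineral density. Blood pressure is listed only as a measurement, together with the number, classes and doses of antihypertensive drugs.

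Table 1 schedules the measured variables at inclusion and again in follow-up:

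- **M3, M6, M12, M18 and M24:** blood pressure, calcium, phosphate, urinary calcium and eGFR.
- **M12 and M24:** PTH, HbA1c, the urinary protein and microalbumin ratios, and echocardiography.
- **M24 only:** bone mineral density.

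**The concern.** A patient's baseline value usually predicts the later value. An analysis that does not use it as a covariate leaves explainable variation in the error term, and a chance baseline difference between the arms stays in the estimate. A change score only partly deals with this, because it fixes the slope on baseline at 1 instead of estimating it.

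Centre is a smaller matter of the same kind. Stratified blocks balance the arms within centre, but a test that ignores centre still counts between-centre variation as error.

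What is at stake is the precision of supportive outcomes. Some of them carry weight here: Table 1 marks calcium, phosphate, urinary calcium and echocardiography as safety data, and Objectives makes the cardiovascular safety of the high-dose scheme one of the main objectives.

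**Working it through.** **The plan's own figure.** The article gives no power or precision figure for any quantitative secondary outcome, so there is nothing to reproduce. I take only the 291 evaluable patients per group from Study population and sample size, and do not examine here how that number was reached.

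**Assumptions (not in the article).** Baseline and follow-up have equal SD and correlation r. The treatment difference used for illustration is 0.2 SD of the follow-up value, tested two-sided at 5%. The intraclass correlation (ICC) for centre is 0.01 to 0.10.

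**Step 1: relative variance of the treatment contrast.**

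- Follow-up values only: 1
- Change score: 2(1 − r)
- ANCOVA: 1 − r²
- ANCOVA relative to change score: (1 − r²) / [2(1 − r)] = (1 + r)/2

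| r | ANCOVA vs change score | ANCOVA vs follow-up only |
|---|---|---|
| 0.5 | 0.75 (25% lower) | 0.75 (25% lower) |
| 0.7 | 0.85 (15% lower) | 0.51 (49% lower) |
| 0.9 | 0.95 (5% lower) | 0.19 (81% lower) |

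The two columns move in opposite directions. The more strongly a variable tracks, the less a change score loses and the more a follow-up-only comparison loses.

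**Step 2: the same in power.** Power = Φ(0.2/√(2V/291) − 1.96), with V the relative variance above. For follow-up only, V = 1 and 0.2/√(2/291) = 2.41, so power is Φ(0.45) = 67.5%.

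| r | Follow-up only | Change score | ANCOVA |
|---|---|---|---|
| 0.3 | 67.5% | 53.1% | 71.5% |
| 0.5 | 67.5% | 67.5% | 79.6% |
| 0.7 | 67.5% | 87.6% | 92.2% |
| 0.8 | 67.5% | 96.8% | 98.0% |

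Below r = 0.5 a change score does worse than ignoring baseline altogether. ANCOVA is best in every row.

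**Step 3: centre.** With arms balanced within centre, adjustment lowers the variance to 1 − ICC. The unadjusted test uses too large a standard error, so its true type I error is 2[1 − Φ(1.96/√(1 − ICC))].

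| ICC | Variance saved | Type I error, unadjusted | Power at 0.2 SD, unadjusted | Power at 0.2 SD, adjusted |
|---|---|---|---|---|
| 0.01 | 1% | 4.9% | 67.5% | 67.9% |
| 0.05 | 5% | 4.4% | 67.9% | 69.7% |
| 0.10 | 10% | 3.9% | 68.3% | 72.0% |

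**Step 4: secondary events.** The sample size section expects 3% to 7% incidence for each component of the composite. Among 640 patients that is 0.03 × 640 ≈ 19 to 0.07 × 640 ≈ 45 events. Recruitment and follow-up "are currently conducted in 30 transplantation departments in France", so this is about 19/30 = 0.6 to 45/30 = 1.5 events per centre. Strata this sparse show no gain from centre-stratified log-rank or Gray tests.

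**The case against.** The strongest reply is that this is one generic sentence in a condensed article. It names families of tests, and the model terms may be set in a full protocol or analysis plan that is not shown. Variance analysis could also be read loosely to include covariance or repeated-measures models. That lowers certainty about what will be done. It does not remove the point, because the article does name a method for these outcomes and, in the same paragraph, states centre adjustment where it wants it.

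A second reply is that no invalid test is proposed. This stands: under 1:1 randomization, change-score, rank and unstratified log-rank comparisons are all valid.

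Three stronger readings are tempting, and the article does not support them:

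- **Baseline is discarded, at a cost of nearly half the information.** At r = 0.7, 1/0.51 = 1.96, as if ANCOVA were worth 96% more patients. That figure compares ANCOVA with follow-up values only. The evolution and change wording covers nearly all the quantitative outcomes, so the fair figure is usually 1/0.85 = 1.18, or 18%.
- **Ignoring centre risks false positives.** The error goes the other way: the unadjusted test is slightly conservative.
- **Every secondary test must be stratified because the primary one is.** Step 4 shows why this does not follow for rare events over 30 centres.

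**Conclusion.** The point holds as a loss of precision in the quantitative secondary outcomes. It is not a bias, and it does not touch the primary analysis, which does account for centre.

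For most outcomes the loss is the gap between change scores and ANCOVA: 5% to 25% of variance for r between 0.9 and 0.5. The larger range of 25% to 81% applies only where follow-up values alone are compared, with blood pressure the likeliest case. The centre term contributes about 1% to 10%, and perhaps less once baseline is in the model, since baseline may absorb some of the centre differences.

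All of these sizes rest on assumed correlations and on equal variance at baseline and follow-up. The direction does not depend on them: in large samples ANCOVA is at least as precise as either alternative at any correlation.

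**What to change.** State that quantitative secondary outcomes will be analysed by ANCOVA with the baseline value as covariate and centre as a fixed or random effect. For variables measured at several follow-up visits, a mixed model with the same terms can be used instead. Log-transform skewed variables before analysis. If covariance analysis was already intended by the present wording, a clarifying phrase is enough.

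Leave the log-rank and Gray tests for the secondary events as they are.

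The cost is a change of analysis wording. Table 1 already schedules every measured baseline value, centre is known from randomization, and neither sample size nor visits change.
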